## Abstract

Introduction: In Germany, stroke is the third leading cause of death, with more than 60,000 fatalities out of approximately 260,000 cases (first-ever and recurrent strokes) each year. So far, there are only a few long-term studies investigating determinants of the natural course of the disease, especially in the era of mechanical thrombectomy. Materials and Methods: The prospective single-center stroke cohort Augsburg (SCHANA) study will include about 1000 patients treated for stroke in the University Hospital of Augsburg. Patients aged 18 years or older with a confirmed diagnosis of ischemic or hemorrhagic stroke are included in the study. Information on demographic characteristics, onset of symptoms, etiologic factors, comorbidities, quality of life, invasive and non-invasive treatment, complications, and laboratory parameters are collected during a personal interview conducted during the patients’ hospital stay and via a medical chart review. About 30 mL of blood is collected from each patient, and after processing and aliquoting, all blood specimens are frozen at −80° C. The study participants will be followed-up via postal questionnaires at three and 12 months after discharge from the hospital. Furthermore, mortality follow-ups will be conducted. Cox-regression analysis will be used to estimate relative risks. Conclusion: The SCHANA study will generate comprehensive data on the long-term course of the disease. In addition to the main outcomes, recurrent events and survival, patient-oriented outcomes such as health-related quality of life and depression are the focus of the study.

## 1. Introduction

According to the World Health Organization (WHO), approximately 15 million people suffer a stroke every year. A high proportion of the cases are fatal, and one-third of stroke patients are affected by a serious, permanent disability [1]. In Germany, stroke is the third-leading cause of death, with more than 60,000 fatalities out of approximately 260,000 cases (first-ever and recurrent strokes) each year [2]. Nearly three-quarters of all strokes occur in people over the age of 65, with the chances of complete recovery or good functional outcome diminishing with increasing age [3]. A high number of stroke survivors suffer post-stroke depression, which is characterized by lethargy, irritability, sleep disturbances, lowered self-esteem, and withdrawal [4]. Up to 10% of people develop seizures following a stroke; the severity of the stroke increases the likelihood of a seizure [5]. The health-related quality of life in stroke survivors shows large variability but is lower than that of the general population [6].

To improve the clinical outcome and recovery of acute ischemic stroke patients, the primary therapeutic goal is the timely restoration of blood flow to salvageable ischemic brain tissue that is not already infarcted [7]. Reperfusion therapy using thrombolysis and endovascular interventions such as mechanical thrombectomy (MT) are the only approved treatments for acute ischemic stroke. If possible, both methods are applied in an overlapping manner (“bridging” therapy), starting with systemic thrombolysis and followed by MT. Still, there are no randomized controlled trials that support additional benefits of tissue plasminogen activator (tPA) application with MT. The current study can help to examine this in more detail in terms of long-term processes and may contribute to exploring bridging therapy in addition to advanced imaging-based approaches to select appropriate patients.

Both thrombolysis and mechanical thrombectomy result in an overall benefit regarding living without disability, but they do not improve survival [8,9]. A portion of patients develop complications after thrombolysis or thrombectomy [10,11], and the neurological recovery is dependent on the patient’s baseline functional status, as well as the status of the brain tissue, as assessed by brain imaging. Thus far, it is not entirely clear which patients are more likely to suffer a complication and which are not. Studies conducted to answer the question of long-term outcome depending on bridging therapy or MT alone were either relatively small, and retrospective [12], or the follow-up period was relatively short (max. of 3 months) with the outcome measures focusing on the modified Rankin Scale alone [13]. The stroke cohort Augsburg (SCHANA) study will help to identify patient groups that are more likely to be affected by post-therapeutic complications.

The clinical distinction between ischemic (IS) (thrombotic or embolic) and hemorrhagic strokes (HS) is of great importance because the management of the various types is very different [3]. Patients with HS require supportive care and have to be monitored for blood pressure control, changes in the level of consciousness, and their blood sugar, and oxygenation must be kept at optimum levels. The prognosis of HS, in general, is worse than for patients with ischemic strokes, but still relatively little is known about the reasons for differences in the acute phase versus long-term outcomes, especially concerning the quality of life in both patient groups in correlation with their functional outcomes. Big registry data are available with the focus on risk factors and outcomes comparing IS and HS, revealing many similarities (age, sex, and hypertension) but also differences in, e.g., smoking and alcohol consumption favoring HS [14]. This highlights the importance of analyzing the risk factors of both IS and HS. However, even large registries focus only on “functional” outcome variables and mortality and omit health-related quality of life, fatigue or depression, and healthcare utilization. Furthermore, studies are increasingly focusing on the identification of biomarkers associated with risk factors and pathogenesis of stroke to make the prevention, diagnosis, and management of stroke more effective [15,16].

The SCHANA study will provide insight into the risk factors, diagnostic procedures, treatment options, and the long-term disease course of a stroke. Furthermore, new knowledge regarding the development, treatment, and prognosis of the disease will be generated by using the information on genetics and –omics data gained from blood samples. In addition, subgroup differences regarding treatment effects and patient outcomes such as long-term survival and recurrent events will be assessed. Patient-oriented outcomes such as quality of life, the burden of depressive disorders, and the extent of disability in patients with stroke will be investigated. Patient subgroups who would benefit from certain (novel) therapies will be identified, and knowledge about the safety and harm associated with the use of drugs will be generated. Specifically, the study will address the following aims:

### 1.1. Primary Outcome

To estimate the impact of thrombolysis, mechanical thrombectomy and drug treatment, comorbidity, treatment-related complications on stroke-related long-term survival, and to examine the frequency and time point of recurrent events; to examine interaction effects between thrombolysis, mechanical thrombectomy and drug treatment on the outcome.

### 1.2. Secondary Outcomes

To identify factors which are associated with the natural course of the disease.To identify subgroups of stroke patients (by clinical, physiologic, or psychologic features) and to assess optimal in-hospital and outpatient treatment for these subgroups.To explore the requirements of bridging therapy (thrombolysis and mechanical thrombectomy).To evaluate the long-term health-related quality of life and the presence of emotional problems, anxiety and/or depression in stroke patients.To measure and monitor the safety and harm associated with the use of thrombolysis, mechanical thrombectomy, and drug treatments in hospital and after discharge.To investigate the role of blood biomarkers (e.g., inflammatory parameters, adipokines) and of “omics” information (genome, metabolome, and proteome data) in disease development, progression, and outcomes.To determine the health care utilization of patients with stroke, and to determine differences in health care utilization according to age, gender, socio-economic status, and place of residence (urban vs. rural).

## 2. Methods and Analysis

The study includes all consecutive adult patients (18 years and older) with incident as well as recurrent ischemic and hemorrhagic stroke who are admitted to the University Hospital of Augsburg. After finishing the pilot study (July/August 2018), the main study began on 1 September, 2018, and is expected to end on 31 December, 2020 (recruitment phase and follow-up).

Participation in the study is voluntary, and a written, informed consent form has to be signed by patients who are willing to take part in the study. If a patient suffers from dementia or another disease with major restrictions, written informed consent is obtained by the responsible legal caregivers, and in this case, a proxy interview is conducted. An extra study information and consent form is provided for the legal caregivers. Patients with language difficulties are asked whether a relative is available for translating the consent form and answering the questions. If this is not possible, patients who are not able to understand the study information and consent form due to language difficulties, are excluded from the study. No further exclusion criteria are set. Patients with post-stroke cognitive impairment (defined by a mini-mental state examination score lower than 27) [17] are included in the study, but will be excluded from certain data analyses, which are exclusively based on questionnaire data provided by the patient.

This is also the case for the follow-up questionnaires. For patients with major restrictions, the responsible legal caregiver will receive the follow-up questionnaires to help the patient with filling in the questions or to answer the questions as a proxy.

At the University Hospital of Augsburg, a high number of stroke patients are treated-yearly about 1500 cases. Based on the experience in previous, comparable studies, it is expected that about 70 percent of these patients will participate. Data collection procedures are performed in accordance with the Declaration of Helsinki.

### 2.1. Data Collection at Baseline Hospital Stay

#### 2.1.1. Patient Interview and Chart Review

Trained study nurses prospectively record all stroke cases. Once the patients are on the general ward, they are informed about the study by a study nurse, who also delivers the study documents. Patients receive comprehensive and understandable information on the processes and consequences of participation in the study.

After the patients have signed the consent form, they are interviewed by a study nurse. In the interview, demographic information, symptoms upon presentation, diagnosis, predisposing and life-style factors, and co-morbidities (e.g., carcinoma, cardiac comorbidity, diabetes mellitus) are assessed. Clinical data on comorbidities, risk factors, medication prescribed prior to the hospital stay and at hospital discharge, diagnostic procedures, clinical characteristics, disabilities, laboratory parameters, and treatment regimens during the hospital stay are assessed by chart review (Table 1).

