## 6. Discussion

In this manuscript, the protocol for a long-term prospective observational cohort study, including patients with acute stroke treated in a hospital, is presented. In this study, the factors associated with the long-term course of this patient group will be investigated. At baseline, data on comorbidities, lifestyle factors, invasive and non-invasive diagnostic and treatment procedures as well as complications during a hospital stay is collected by a personal interview and a chart review. Three and twelve months after hospital discharge, follow-up data will be gathered via postal questionnaires. Furthermore, cause-specific mortality will be assessed through regular mortality follow-up.

Strengths of the present study are the large sample size, the generation of a considerable amount of data, in particular outcome data, and the long-term aspect of the study. Furthermore, data on the occurrence of the acute event are gathered through a face-to-face interview with the patients. Finally, from the study participants, blood is collected and stored. However, the study also has limitations. It is possible that selection bias will occur because patients who are more ill may refuse participation in the study. The present study is designed as a single-center and not as a multicenter study. Finally, another limitation is expected to be a loss to follow-up and the occurrence of missing data.

Altogether, the SCHANA study will add to the current knowledge on the long-term course of stroke and its subtypes. Through this study, prognostic factors regarding different outcomes will be examined. Due to the availability of blood specimens, novel biomarkers which may be associated with the disease course can be identified. Therefore, the results of the study might help guide the various disciplines involved in treating patients with stroke.

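### Consent is sought on the general ward, so patients who die before then cannot enter a cohort described as consecutive admissions and meant to show how treatment affects survival

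*Protocol article*

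**What the plan says.** Section 2 (Methods and Analysis) defines the population broadly: "The study includes all consecutive adult patients (18 years and older) with incident as well as recurrent ischemic and hemorrhagic stroke" admitted to the hospital. After an exclusion for language difficulties that no relative can bridge, it adds: "No further exclusion criteria are set".

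Section 2.1.1 describes how people enter: "Once the patients are on the general ward, they are informed about the study by a study nurse". It continues: "After the patients have signed the consent form, they are interviewed by a study nurse". Section 5 (Ethics and Dissemination) makes consent a condition of inclusion, with a legal caregiver as the only substitute. For patients with dementia or another disease with major restrictions, section 2 provides that "written informed consent is obtained by the responsible legal caregivers, and in this case, a proxy interview is conducted"; it gives no earlier time or other place of approach for them. Section 2.1.1 also states: "Trained study nurses prospectively record all stroke cases".

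The primary aim in section 1.1 is "To estimate the impact of thrombolysis, mechanical thrombectomy and drug treatment, comorbidity, treatment-related complications on stroke-related long-term survival". Section 1.2 adds the safety and harm of thrombolysis, thrombectomy and drug treatment, explicitly including the hospital stay. On selection, the Discussion says: "It is possible that selection bias will occur because patients who are more ill may refuse participation in the study".

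**The concern.** Reaching the general ward alive and being consented there is an entry condition that section 2 does not list. Thrombolysis and thrombectomy are acute treatments, and Table 1 has an item for intensive care or stroke unit treatment, so part of the treatment pathway lies before the point of approach. Entry to the cohort is then conditional on something that happens after treatment and that treatment may influence.

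At stake are the treatment and complication effects on survival and the in-hospital safety results. A death before consent is missing from both the numerator and the denominator. If pre-ward death differs by treatment, by complication or by stroke type, comparisons in the enrolled cohort differ from those in all admitted patients, and no adjustment of the enrolled data recovers the missing deaths. Later quality of life and health care use among survivors are much less exposed.

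**Working it through.** **Step 1: set the sections side by side.**
- Stated population (section 2): every consecutive admitted adult with stroke, with language as the only exclusion.
- Route of entry (sections 2.1.1 and 5): information on the general ward, then consent by the patient or a legal caregiver; without consent, no inclusion.
- Consequence: a patient who dies before ward approach and consent meets the stated criteria but cannot become a participant. The two descriptions do not agree.
- Still captured: a complication that becomes fatal after enrolment, and an earlier non-fatal one, because in-hospital complications are a baseline item in Table 1 and clinical data come from chart review.

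**Step 2: look for a figure to reproduce.** There is none on this point. The article states no pre-ward death rate and no survival figure for this cohort. The sample size of 997 in section 4 rests on stroke recurrence and is not in dispute here. All mortality inputs below are assumptions.

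**Step 3: treatment effect.** Let a be the risk of death before the ward and b the later mortality among those who reach it, with subscript 1 for treated and 0 for untreated patients. Mortality from admission is 1 − (1 − a)(1 − b). The ratio in all admitted patients is [1 − (1 − a₁)(1 − b₁)] / [1 − (1 − a₀)(1 − b₀)]; the ratio in the enrolled cohort is b₁/b₀. This takes the enrolled patients as representative of those who reach the ward and leaves confounding aside.

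Assume b₁ = b₀ = 15% and a₀ = 6%. Untreated mortality is 1 − 0.94 × 0.85 = 20.1%.

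| Pre-ward death, treated | Mortality from admission, treated | Ratio, all admitted | Ratio, enrolled |
|---|---|---|---|
| 3% | 1 − 0.97 × 0.85 = 17.55% | 0.87 | 1.00 |
| 6% | 1 − 0.94 × 0.85 = 20.1% | 1.00 | 1.00 |
| 10% | 1 − 0.90 × 0.85 = 23.5% | 1.17 | 1.00 |

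The enrolled cohort shows no effect in all three rows, whether treatment lowers, leaves unchanged or raises early death.

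**Step 4: a case where later mortality differs.** Assume a₀ = 5%, b₀ = 10% and b₁ = 8%. Untreated mortality is 1 − 0.95 × 0.90 = 14.5%. For a₁ = 5%, 8%, 10% and 15%, treated mortality is 12.6%, 15.36%, 17.2% and 21.8%, and the ratios in all admitted patients are 0.87, 1.06, 1.19 and 1.50. The enrolled cohort shows 0.08/0.10 = 0.80 each time. Even with equal pre-ward death (5% and 5%) the two ratios differ, 0.87 against 0.80, because they refer to different populations.

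**Step 5: complications.** Assume a complication in 6% of patients, pre-ward death of 4% without it, and later mortality of 15% with it and 10% without. Mortality without it is 1 − 0.96 × 0.90 = 13.6%. If pre-ward fatality with the complication is 10%, 30% or 50%, mortality with it is 23.5%, 40.5% or 57.5%, and the ratios are 1.73, 2.98 and 4.23. The enrolled cohort shows 0.15/0.10 = 1.50 each time. The observed complication frequency falls from 6% to 5.7%, 4.5% or 3.2%; for example, 0.06 × 0.70 / (0.06 × 0.70 + 0.94 × 0.96) = 4.5%.

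**The case against.** The strongest reply is that this is a condensed article and that survival among patients who reach the ward is a legitimate target for an aim worded as long-term survival. The Discussion already concedes selection against sicker patients, caregiver consent brings in severely impaired survivors, the nurses record every stroke case, and the enrolment chart in Figure 1, which is not visible here, may show losses before consent.

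Much of this stands. Conditional survival is a valid target if it is named, and it cannot be said that a screening count is missing. But the aims do not name it, and the safety aim reaches into the hospital stay. Refusal is a different mechanism from death before approach. Caregiver consent has no earlier point of approach and cannot bring in those already dead. Nothing says that recorded cases without consent contribute outcome data.

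Four stronger readings are tempting and not supported:
- That the survival analysis already contains immortal time. Section 3 names Cox regression without a time origin and does not rule out delayed entry, and an analysis plan commonly settles this. The problem would arise only if time started before entry without delayed entry.
- That the design hides early harm. The direction is unknown: fewer pre-ward deaths among treated patients would hide an early benefit instead.
- That no fatal complication is ever captured. Only those fatal before ward consent are lost.
- That section 2.1.1 allows a single approach to each patient. Its wording means as soon as the patient is on the ward.

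**Conclusion.** The point holds as a conflict between the stated population and the described route of entry, with consequences for the primary survival aim and the in-hospital safety aim. Patients who die before ward approach and consent cannot be enrolled, and the article neither lists this as an exclusion nor names it as a limitation.

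The size cannot be read from the documents. Under the assumptions in Step 3, ratios of 0.87 to 1.17 in all admitted patients all appear as 1.00 in the enrolled cohort; under those in Step 5, complication ratios of 1.73 to 4.23 appear as 1.50. These figures show what the design cannot distinguish; they do not predict the study's result. The discrepancy is small if few patients die before the ward. The documents also give no figure showing that hemorrhagic stroke is affected most, although the Introduction describes its prognosis as generally worse. The matter should be corrected, but it does not undermine the study as a whole.

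**What to change.** 1. In section 2, describe the cohort as patients alive and consented on the general ward, and restrict the survival aim in section 1.1 and the in-hospital safety aim in section 1.2 to that population.
2. From the nurses' existing record of all stroke cases, and as ethics approval permits, report aggregate counts of pre-ward deaths and of non-consenters by age, sex, stroke type and reperfusion treatment. Use them in a bounding sensitivity analysis of the treatment effects, for example by putting the observed pre-ward death proportions into the Step 3 formula and varying the unknown outcomes of non-consenters.
3. Start Cox time at enrolment or, if time starts at admission, let each patient enter the risk set at consent. State that this avoids immortal time but does not recover pre-ward deaths, and that it assumes the time of entry is uninformative, which is doubtful if slower transfer to the ward reflects severity.
4. Add death before approach to the limitations in the Discussion, next to refusal.

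The cost is a narrower claim, one small table, possibly an entry-time variable, and ethics confirmation for the aggregate counts. Recruitment procedures and the sample size calculation need not change.

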#### 2.1.2. Collection of Biomaterial

During the hospital stay, about 30 mL of blood is collected from each patient. The blood samples are processed and aliquoted into sample tubes according to a standardized procedure. The aliquots are subsequently frozen at −80 °C and stored. It is planned to measure pro- and anti-inflammatory cytokines (e.g., interleukin (IL)-6, tumor necrosis factor (TNF)-alpha, IL-4, IL-10), adipokines (e.g., adiponectin, chemerin), neuroimmunokines (e.g., brain-derived growth factor, neurotrophins) and metabolomics in blood samples

### 2.2. Follow-Up of the Stroke Patients

#### Morbidity Follow-Up and Update of Treatment, Lifestyle and Health Factors

Three and 12 months after hospital discharge, all study participants will receive postal questionnaires or telephone interviews. The postal questionnaires will include questions on disease symptoms, complications, disabilities and comorbidities; behavioral and clinical risk factors (smoking, alcohol consumption, body weight, height); physical activity (German-PAQ-50+) [18]; health-related quality of life (Stroke Impact Scale) [19,20,21] and EQ-5D [22,23]; fatigue and headache (Rostock Headache Questionnaire) [24]; vertigo and depression (PHQ-9) [25,26]; recurrent events, bleeding outcomes, and healthcare utilization (readmissions, visits to physicians, clinics, and emergency departments); and data on current medication. An overview of the data collected at baseline and follow-up is given in Table 1, and a study flow-chart with enrollment and follow-up is depicted in Figure 1.

